## Abstract

Operating room nurses may experience occupational burnout brought by noise annoyance during which emotional labor may act as a moderating factor between the two. The aims of this study are: (1) to investigate the independent correlation between noise annoyance and burnout among operating room nurses; (2) to explore the relationship between noise annoyance, emotional labor, and burnout. This study, a cross-sectional study design, is being conducted in Guizhou province, China. The Chinese version of the noise annoyance, emotional labor and burnout scale will be used to assess the current situation of the samples, and the data will be collected using paper questionnaires and electronic questionnaires. Additionally, the Pearson or Spearman rank correlation coefficients will be involved in correlation analyses. Multiple linear regression analysis will be also carried out to produce *β*-coefficients with 95% confidence intervals. A nonparametric, bias-corrected 95% bootstrapped confidence interval with 5,000 bootstrap iterations will help to determine the importance of mediating effects. The trial registration number is ChiCTR2300068414.

## Introduction

Burnout represents a significant challenge to the well-being of nurses and their professional environment [1]. Defined as a prolonged response to chronic interpersonal and emotional stressors in the workplace, burnout is a complex occupational psychosocial syndrome [2]. In mainland China, the prevalence of burnout among registered nurses is alarmingly high, reaching up to 50% [3]. Operating Room (OR) nurses, due to the high-intensity, high-risk, and overload of their work, are particularly vulnerable to burnout [4]. A study conducted by Ren Lanzhu reported that 78.77% of OR nurses experience varying degrees of burnout [5]. The implications of burnout extend beyond individual well-being, affecting nurses’ physical and mental health, increasing turnover intentions, and negatively impacting care quality, patient safety, and job satisfaction [6]. Moreover, research indicates that burnout among nurses correlates with higher patient mortality rates and increased hospital-acquired infections [7]. Therefore, exploring the factors contributing to burnout in OR nurses and identifying effective intervention strategies are crucial for improving their mental health.

Noise annoyance (NA) is defined as the adverse emotional response of individuals or groups exposed to noisy environments. It manifests through feelings of distraction, discomfort, irritation, and anxiety, serving as one of the most significant psychological impacts of noise [8,9]. Noise annoyance is widely regarded as a key indicator of adverse subjective reactions to noise. OR nurses are likely to experience heightened levels of noise annoyance due to their work environment. A study revealed that 95.2% of anesthesiologists working in ORs reported annoyance caused by noise, with 14.5% experiencing high levels of noise annoyance [10]. Furthermore, burnout is closely linked to negative emotional states [11]. Noise annoyance, an often overlooked negative emotion [12], may be significantly associated with burnout. However, the precise relationship between noise annoyance and burnout remains underexplored, warranting further investigation.

Emotional labor (EL) refers to the process by which individuals regulate their emotions to align with organizational expectations, resulting in specific facial expressions and behavioral displays required by their roles [13]. OR nurses frequently engage in emotional labor to provide patient care [14]. Bartram confirmed that emotional labor is a significant positive predictor of burnout [15]. And negative emotions are one of the factors influencing emotional labor [16]. Since noise annoyance is a form of negative emotion [12], the relationship between noise annoyance and emotional labor in OR nurses has yet to be explored.

While the relationship between emotional labor and burnout appears well-established, the link between noise annoyance and burnout remains unclear, and the role of emotional labor in the connection between noise annoyance and burnout is still unknown. Therefore, the objectives of this study are: (1) to investigate the independent correlation between noise annoyance and burnout among OR nurses; (2) to explore the relationship between noise annoyance, emotional labor, and burnout.

### Research hypothesis

As early as 1988, Topf identified noise pollution as a significant stressor in the nursing work environment, with noise-induced stress serving as a predictive factor for burnout among clinical nurses [17]. Noise annoyance, as a specific form of psychological stress [18], may influence the onset of burnout, particularly given the well-established link between stress and burnout [19]. In addition, a survey of 2,000 nurses in Taiwan examining burnout identified feelings of tension, irritability, sadness, inferiority, and sleep disturbances as the most significant predictors of burnout [20]. Compared to factors such as job satisfaction, job engagement, and work environment, psychological factors were found to have the most substantial correlation with emotional exhaustion [13,14]. Negative emotions have also been shown to correlate positively with burnout [11]. From a psychological perspective, noise annoyance in OR nurses represents a form of negative emotion [18], which may, in turn, contribute to burnout.

The Conservation of Resources theory posits that the persistent threat of resource loss can lead to burnout, ultimately impacting patient safety [19]. This theory is grounded in the premise that individuals strive to acquire, maintain, and protect resources they value, providing a useful framework for understanding burnout. It highlights the psychological stress experienced by workers in human services, including healthcare and education, as a result of interpersonal demands [21,22]. For OR nurses, exposure to noise annoyance can deplete emotional resources, and if these resources are not replenished in a timely manner, further depletion may lead to burnout.

Grandey identified several factors influencing emotional labor, including emotional intelligence, emotional expression, emotional disposition, and emotional events (both positive and negative) [23]. And negative emotions are significantly correlated with emotional labor [16], which is considered a key predictor of burnout [24]. The Self-Regulation Theory refers to the process by which individuals control or alter their thoughts, emotions, impulses, and behaviors to achieve specific goals [25]. In the context of emotional labor, OR nurses adjust and display appropriate emotions to meet work requirements or objectives, exemplifying a typical self-regulation process. Before engaging in emotional labor for patients, OR nurses may already be experiencing varying degrees of noise annoyance. The higher the level of noise annoyance, the more pronounced the emotional dysregulation, which increases the likelihood of emotional exhaustion and ultimately leads to burnout. Furthermore, when OR nurses engage in emotional labor, noise annoyance forces them to exert more self-regulation, thereby increasing the demand for emotional resources. When emotional demands and resources are significantly out of balance, burnout is likely to accelerate.

Based on these considerations, this study proposes the following hypotheses:

a) There is a positive correlation between noise annoyance and burnout among OR nurses.b) There is a positive correlation between noise annoyance and emotional labor among OR nurses.c) There is a positive correlation between emotional labor and burnout among OR nurses.d) Emotional labor mediates the relationship between noise annoyance and burnout among OR nurses.

The hypothesized model for this study is illustrated in Fig 1.

**Fig 1 pone.0321731.g001:**
[figure not shown]
The conceptual framework of the relationship between noise annoyance, emotional labor and burnout.

## Materials and methods

### Study design and setting

We will conduct this descriptive, cross-sectional study on a convenience sample in ORs of 11 hospitals in Guizhou Province, China. These hospitals are all tertiary hospital with more than 500 beds.

### Participants

Participants will be recruited from 11 hospitals in accordance with the criteria below. The inclusion criteria are: (1) Registered nurses who have worked in ORs for more than 1 year; (2) They should work in the corresponding post in ORs during the investigation period; (3) They provide informed consents and voluntary participation in this study. Visiting fellowship nurses and practical nurses will be excluded in our study.

The required sample size was calculated using G*Power 3.1.9.7 software [26] for multiple linear regression analysis, with four predictor variables: noise annoyance, surface acting, deep acting, and natural emotional expression, and burnout as the outcome variable. While emotional labor is our primary construct of interest, it is operationalized through three distinct dimensions—surface acting, deep acting, and natural emotional expression—each serving as an individual predictor. This differentiation allows for a more nuanced examination of how each aspect of emotional labor contributes to burnout among OR nurses.

The test family used was F-tests, and the statistical test employed was linear multiple regression (Fixed model, R² deviation from zero). A priori: Compute required sample size - given α, power, and effect size, was used for the type of power analysis. Assuming a medium effect size (f² = 0.15), an alpha level of 0.05, and a desired power of 0.95, the minimum required sample size was determined to be 129 participants. To account for a potential 20% dropout rate, the final minimum sample size was calculated to be 155. This sample size ensures sufficient power to detect significant relationships within our multiple regression model [27].

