Potential confounders as contributors to burnout, and possibly related to noise annoyance and emotional labor, were defined a priori and incorporated into the statistical model, such as sex, age, marital status, education level, personality traits, health status, work experience as an operating room nurse, professional title, annual income, satisfaction with salary and hospital tenure. We will carry out linear multiple regression analysis to control for confounders and determine whether noise annoyance and emotional labor are contributors to burnout. Before performing multiple regression analyses, we will examine scatterplots of each predictor variable against the burnout score to check for linear relationships. The normality of residuals will be tested using the Shapiro-Wilk test and visualized with Q-Q plots. And we will evaluate homoscedasticity by plotting residuals versus predicted values. The Durbin-Watson statistic will be used to test for autocorrelation of residuals. In case non-linear relationships are identified, we will consider applying transformations to the predictor variables or incorporating polynomial or interaction terms into the regression model to better capture the nature of the relationships.

To address the risk of multicollinearity arising from multiple confounders, we will calculate Variance Inflation Factors (VIF) and tolerance levels for each predictor variable. A VIF value exceeding 5 or a tolerance value below 0.2 will indicate significant multicollinearity [39]. If multicollinearity is detected, we will consider removing highly correlated variables.

We will use Model 4 (PROCESS macro) in SPSS 26.0 to examine the mediation effect of emotional labor on the relationship between noise annoyance and burnout among OR nurses [40]. A nonparametric, bias-corrected 95% bootstrapped confidence interval (BCI) with 5,000 bootstrap iterations will be used to determine the importance of mediating effects. Indirect effects will be deemed significant if the 95% BCI do not contain zero [41,42]. A p-value of 0.05 or lower will be regarded as statistically significant, based on a two-sided test.

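### The 0.95 power belongs to an overall F-test of a four-predictor model; the planned model has at least 15 predictors, and power for hypotheses a–d is not established

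*Protocol article*

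**What the plan says.** Under Participants, the protocol article describes a G*Power calculation for a regression "with four predictor variables: noise annoyance, surface acting, deep acting, and natural emotional expression, and burnout as the outcome variable". It names the test: "the statistical test employed was linear multiple regression (Fixed model, R² deviation from zero". The inputs are given as "Assuming a medium effect size (f² = 0.15), an alpha level of 0.05, and a desired power of 0.95", with the result that "the minimum required sample size was determined to be 129 participants". After a 20% allowance the target becomes 155. The paragraph ends: "This sample size ensures sufficient power to detect significant relationships within our multiple regression model".

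Under Statistical analysis, the regression is wider. Potential confounders "were defined a priori and incorporated into the statistical model, such as sex, age, marital status, education level, personality traits, health status", and the list goes on to operating-room experience, professional title, annual income, satisfaction with salary and hospital tenure. That makes eleven named variables, introduced as examples.

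Under Research hypothesis, a–c are pairwise positive associations among noise annoyance, emotional labor and burnout, and d is mediation by emotional labor. Mediation is judged by whether a bias-corrected bootstrap 95% interval excludes zero.

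**The concern.** The power statement and the analysis describe different models and different tests.

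- **Model.** The calculation counts four predictors. The planned regression has 4 + 11 = 15 at least, and more once multi-category confounders are coded.
- **Test.** The overall F-test asks whether anything in the model predicts burnout. It can reject because of emotional labor or a confounder alone, with no noise-annoyance effect. Its power is therefore not the power of the noise-annoyance coefficient, and it says nothing direct about the indirect effect.

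The 0.95 is attached to the study's own regression model. A reader who meets a null noise-annoyance coefficient or a null indirect effect could take it to come from a study with 95% power for that question. The article does not show this.

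**Working it through.** **Inputs.** From Participants: overall F-test, 4 predictors, f² = 0.15, alpha 0.05, power 0.95, N = 129, then 155. From Statistical analysis: 11 named confounders. From Variables: personality has 5 answers, health 4, salary satisfaction 3; levels of the other categorical confounders are not given.

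**Formula.** Power = P(F′ > F crit), where F′ is noncentral F with df1 = predictors tested, df2 = N − total predictors − 1 and λ = f² × N.

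**1. The plan's figure.** df1 = 4, df2 = 129 − 4 − 1 = 124, λ = 0.15 × 129 = 19.35. Power is 0.951, so 129 reproduces. The 155 is 129 × 1.20 = 154.8, rounded up.

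**2. Predictor count.** With one term per confounder: 4 + 11 = 15. Dummy-coding only the three confounders with stated levels gives 4 study predictors + 8 single-term confounders + (4 + 3 + 2) dummies = 21. With emotional labor as one total score and one term per confounder: 2 + 11 = 13.

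**3. Same overall test, total f² held at 0.15.**

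| Predictors | Power, n = 129 | Power, n = 155 | N for 0.95 |
|---|---|---|---|
| 4 | 0.95 | 0.98 | 129 |
| 13 | 0.79 | 0.88 | 189 |
| 15 | 0.76 | 0.86 | 199 |
| 21 | 0.67 | 0.78 | 226 |

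The n = 155 column supposes that no questionnaire is lost.

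**4. If the confounders explain further variance (assumed amounts).** f² = 0.15 means R² = 0.15 / 1.15 = 0.130. Adding 0.05 gives R² = 0.180 and f² = 0.180 / 0.820 = 0.220. With 15 predictors, power is then 0.93 at n = 129 and 0.97 at n = 155. Adding 0.10 gives R² = 0.230, f² = 0.299, and power 0.986 and 0.997.

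**5. f² = 0.15 read as the joint increment of the four study predictors over eleven confounders.** df1 = 4, df2 = 129 − 15 − 1 = 113. Power is 0.950 at n = 129, and 130 are needed to reach 0.95 strictly. The stated power is kept.

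**6. Noise-annoyance coefficient alone, 15 predictors.** df1 = 1, df2 = 113 at n = 129.

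| Partial f² (assumed) | Power, n = 129 |
|---|---|
| 0.15 | 0.99 |
| 0.10 | 0.945 |
| 0.05 | 0.71 |
| 0.0375 (0.15 split equally over four) | 0.59 |
| 0.02 | 0.36 |

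The extra covariates hardly matter here: at 0.0375, power is 0.588 with 4 predictors and 0.587 with 15. The unstated partial effect is what matters.

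**7. Detectable partial f² for one coefficient, 15 predictors.** At n = 155: about 0.051 (80% power) and 0.085 (95%). At n = 129: about 0.062 and 0.103.

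**8. Indirect effect.** The article gives no path sizes. As an illustration only, a joint-significance approximation at n = 129 (direct path 0.14, covariates unrelated to the paths, both assumed) gives power 0.40 for two standardised paths of 0.20, 0.73 for 0.26 and 0.88 for 0.30.

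**The case against.** The strongest reply is that the study may be adequately powered all the same.

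- Holding total f² at 0.15 while adding eleven predictors treats the confounders as explaining nothing, although the article selects them as contributors to burnout. This stands: 0.76 is the figure under that assumption, not a settled shortfall, and step 4 shows how fast it recovers.
- If 0.15 belongs to the four study predictors, the increment test keeps 0.95. This also stands, but it is not the test the article names.
- The 0.59 for a single coefficient rests on an equal split that no passage supports; at a partial f² of 0.15 the power is 0.99. This stands as well, so only the range can be reported.
- Hypotheses a–c are worded as correlations, and Pearson or Spearman coefficients are planned. By Fisher's z, a two-sided Pearson test at n = 129 has power 0.82 for r = 0.25 and 0.94 for r = 0.30. This is fair: the unadjusted correlations may be well served. They are still not what the calculation covers.
- The 155 is called a minimum, so more nurses may be enrolled. That would help, but it does not repair the statement.

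A reader might infer from all this that the 0.95 is simply not delivered, or that true power is 0.6 to 0.7. The document does not support that, because the inputs that would decide it are absent. Nor does it support a count of about 25 predictors, since the levels of title, education and marital status are not given.

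**Conclusion.** The point holds in a limited form. The 129 is correct for its own inputs; the fault is in what it is applied to. The 0.95 refers to a four-predictor overall test, which is neither the planned model nor a test of any of hypotheses a–d.

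- For the stated test on the planned model, power is 0.76 at n = 129 and 0.86 at n = 155 with 15 predictors (199 needed), and 0.67 and 0.78 with 21 (226 needed), provided total f² remains 0.15. It is 0.93 at n = 129 with 15 predictors if the confounders add R² of 0.05.
- For the four study predictors jointly over eleven confounders, f² = 0.15 still gives 0.95.
- For the noise-annoyance coefficient, power is undetermined: 0.59 to 0.99 at n = 129 as partial f² goes from 0.0375 to 0.15, both assumed values.
- For the indirect effect, no sample-size basis is given.

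The claim of sufficient power for the regression model is therefore unsupported as written, and it should be corrected because readers will rely on it when interpreting null results.

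**What to change.** Replace the closing sentence of the sample-size paragraph, and do not claim 0.95 for hypotheses a–d. Then:

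1. Either restate the calculation for the planned test (an R² increase with noise annoyance as the one tested predictor), giving the tested and total numbers of predictors after coding and saying what f² refers to; or keep the size and report the detectable effect. With 15 predictors that is a partial f² of about 0.051 (80% power) and 0.085 (95%) at n = 155, or 0.062 and 0.103 at n = 129.
2. Add a simulated power for the bias-corrected bootstrap indirect effect over a stated range of path sizes, at the expected number of evaluable questionnaires.

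The cost is one rewritten paragraph and a short simulation. No participants are added and no analysis changes; the stated power may become less favourable.

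### The minimum of 155 does not cover the stated 20% loss: it leaves 124 usable questionnaires, against the 129 the plan requires

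*Protocol article*

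**What the plan says.** The sample size is set in the protocol article, Materials and methods, Participants. The calculation is an F test for "linear multiple regression (Fixed model, R² deviation from zero"), "with four predictor variables: noise annoyance, surface acting, deep acting, and natural emotional expression", and burnout as the outcome. The remaining inputs are "Assuming a medium effect size (f² = 0.15"), "an alpha level of 0.05" and "a desired power of 0.95". From these, "the minimum required sample size was determined to be 129 participants". The next sentence adds the loss allowance: "To account for a potential 20% dropout rate, the final minimum sample size was calculated to be 155". The section closes by stating that this number gives enough power for the regression model.

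The inflation formula is not printed, and no other section gives a different loss rate or final number. The Statistical analysis section shows where losses would arise in this one-time survey: returned questionnaires are checked for completeness, and those with patterned or uniform answers are deleted as invalid.

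**The concern.** Three figures in one paragraph do not fit together: 129 needed, 20% lost, 155 enrolled. The 155 looks like 129 increased by a fifth. That is a common slip, because 20% of the larger, enrolled number is more than 20% of the smaller, analysable number. If so, the published minimum fails to deliver the analysable sample it was meant to protect, under the plan's own loss assumption. The power of 0.95 would then not be reached even for the four-predictor test behind the calculation.

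**Working it through.** **Inputs, all from the Participants section:** 4 predictors; f² = 0.15; alpha 0.05; target power 0.95; required number 129; loss rate 20%; final minimum 155.

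**Step 1: reproduce 129.** For the test that R² is zero with u predictors, the numerator degrees of freedom are u = 4, the denominator degrees of freedom are v = N − 5, and the noncentrality is λ = f² × N. Power is the probability that a noncentral F(u, v, λ) variable exceeds the upper 5% point of the central F(u, v).

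| N | v | λ = 0.15 × N | Power |
|---|---|---|---|
| 128 | 123 | 19.20 | 0.9489 |
| 129 | 124 | 19.35 | 0.9506 |

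The smallest N with power of at least 0.95 is 129. The plan's figure is reproduced exactly and has no slack: one participant fewer already falls below the target.

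**Step 2: reproduce 155.** 129 × (1 + 0.20) = 154.8, rounded up to 155. This matches the plan. The use of this formula is inferred from the match, since the article does not print it.

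**Step 3: apply the stated loss to 155.** 155 × (1 − 0.20) = 124, which is 129 − 124 = 5 short. This step does not depend on how 155 was obtained.

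**Step 4: the number that does cover a 20% loss.** 129 / (1 − 0.20) = 161.25, rounded up to 162. Check: 162 × 0.80 = 129.6, which meets 129, while 161 × 0.80 = 128.8 does not. The difference from the plan is 162 − 155 = 7.

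**Step 5: the loss that 155 does cover.** 155 − 129 = 26 questionnaires, and 26 / 155 = 16.8%.

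**Step 6: the effect on power.** At N = 124, v = 119 and λ = 0.15 × 124 = 18.60, giving power 0.9415. Against 0.9506 at N = 129, this is a drop of 0.0091, or about 0.9 percentage points.

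**The case against.** The strongest reply is that this changes almost nothing. Power of 0.94 is still high, and no estimate, test or hypothesis is affected. That is correct, and it limits the weight of the point.

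Second, 155 is described as a minimum. Recruitment is by convenience sampling in 11 tertiary hospitals with no stated cap, so the shortfall to 124 occurs only if enrolment stops at 155 and the full 20% is lost. This also stands as a description of what may happen in practice. But a stated minimum is the number at which the guarantee has to hold, and here it does not.

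Third, dropout is not defined and the formula is not shown; the authors may have meant a 20% margin on top of 129. On that reading 155 is the right sum, but the sentence would then describe a margin and not a dropout rate. In its ordinary meaning a dropout rate is a share of those enrolled, and deletion of invalid questionnaires from those returned works in just that way.

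Fourth, according to the Measurement section the formal survey began in March 2023 and was scheduled to run to the end of July 2023, so changing the target may come too late. That bears on the choice of remedy and not on whether the figure is right.

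Last, 162 rests on the same four-predictor calculation as 129, whereas the Statistical analysis section adds eleven named confounders and a bootstrap mediation analysis. Correcting the loss allowance does not establish the power of those analyses. This is true, and the correction should not be presented as if it did.

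**Conclusion.** The concern holds. On the plan's own inputs, the stated minimum of 155 leaves 124 analysable questionnaires after a 20% loss, 5 fewer than the required 129; the figure consistent with the stated loss is 162, or 7 more. The consequence is minor: power of 0.941 where the plan claims 0.95, for the four-predictor test only. The conclusion assumes that the 20% is a share of those enrolled and that enrolment stops at the stated minimum. If more are enrolled or fewer are lost, the shortfall shrinks or disappears, but the published sentence remains wrong as written.

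**What to change.** Replace 155 with 162 in the Participants section and show the formula, 129 / (1 − 0.20).

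If recruitment has closed, leave 155 as the historical planning figure and add one sentence. It should say either that 155 allows for the loss of 26 questionnaires (about 16.8%), or that after a 20% loss power would be 0.94 for the four-predictor test of R². State in the same place that the loss means incomplete or invalid questionnaires, since there is no follow-up from which to drop out.

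The cost is one number or one sentence, and at most 7 more questionnaires across the 11 hospitals.

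### The stated pair of 0.95 power and 5% alpha assumes independent nurses, but they come from 11 hospitals and the planned regression ignores hospital

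*Protocol article*

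**What the plan says.** Under Study design and setting, the protocol article describes a "convenience sample in ORs of 11 hospitals in Guizhou Province, China". Under Measurement, the operating-room head nurse of each target hospital recruits the eligible nurses.

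The sample size in the Participants section rests on "linear multiple regression (Fixed model, R² deviation from zero"), "with four predictor variables: noise annoyance, surface acting, deep acting, and natural emotional expression, and burnout as the outcome variable". The inputs are given as "Assuming a medium effect size (f² = 0.15), an alpha level of 0.05, and a desired power of 0.95", and "the minimum required sample size was determined to be 129 participants". A dropout allowance follows: "To account for a potential 20% dropout rate, the final minimum sample size was calculated to be 155". The section closes with "This sample size ensures sufficient power to detect significant relationships within our multiple regression model".

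The Statistical analysis section plans ordinary multiple linear regression and PROCESS Model 4 with a bootstrap. Its list of confounders includes hospital tenure, which is a characteristic of the nurse, but not hospital itself. The only check on dependence between residuals is the Durbin-Watson statistic. No ICC or design effect appears anywhere.

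**The concern.** The fixed-model F test treats every nurse as an independent observation. Nurses in one operating-room department share equipment, noise sources and management, so noise annoyance and burnout may both be correlated within hospital. If both are, ordinary regression understates the standard errors and rejects too often. Durbin-Watson does not detect this, because it tests serial order and not grouping.

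At stake is the calibration of the main results. The overall test would be presented as run at 5% with 0.95 power, whereas the true type I error may be higher. Confidence intervals for the regression coefficients may be too narrow, and the mediation analysis, which names no hospital term either, has the same weakness.

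**Working it through.** **Inputs from the Participants and Study design sections.** f² = 0.15, alpha = 0.05, u = 4 predictors, N = 129 (155 with the dropout allowance), k = 11 hospitals.

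**Assumptions, because the documents give no figures.** Equal hospital sizes, so m = 129/11 = 11.73; four mutually uncorrelated predictors with a common ICC ρx; residual outcome ICC ρy; f² defined against total residual variance; confounders left out.

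**Step 1: reproduce the plan's figure.** Noncentrality λ = f²·N = 0.15 × 129 = 19.35 with 4 and 124 degrees of freedom gives power 0.9506. N = 128 gives 0.9489. So 129 is correct under independence and is the smallest size that reaches 0.95.

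**Step 2: type I error of the analysis as planned.** Data were simulated with random hospital effects in predictors and outcome, no true association, and the ordinary F test at 5%.

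**Step 3: power of a hospital-adjusted analysis at N = 129.** The information splits into a within-hospital and a between-hospital part:

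- W = (N − k)(1 − ρx)/(1 − ρy)
- B = (k − 1)(1 − ρx + mρx)/(1 − ρy + mρy)
- Random intercept, ICC treated as known: λ = f²(W + B)·N/(N − 1), with 4 and 124 degrees of freedom
- Hospital fixed effects: λ = f²·W, with 4 and N − k − 4 = 114 degrees of freedom

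Worked case, ρx = 0.3 and ρy = 0.10:

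- W = 118 × 0.7/0.9 = 91.8
- B = 10 × (0.7 + 3.52)/(0.9 + 1.17) = 20.4
- Random intercept: λ = 0.15 × 112.2 × 129/128 = 17.0, power 0.92
- Fixed effects: λ = 0.15 × 91.8 = 13.8, power 0.84

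| Assumed ρx / ρy | Type I error, unadjusted F test | Power, random intercept | Power, fixed effects |
|---|---|---|---|
| 0.1 / 0.05 | about 6% | 0.95 | 0.91 |
| 0.3 / 0.05 | about 8% | 0.92 | 0.82 |
| 0.3 / 0.10 | about 11% | 0.92 | 0.84 |
| 0.5 / 0.10 | about 17% | 0.87 | 0.69 |

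Separate simulation runs of the type I error agree to within about one percentage point.

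**Step 4: settings where the outcome ICC is at least the predictor ICC.** When ρx = ρy, W + B = (N − k) + (k − 1) = N − 1, so λ returns to 19.35 and the random intercept keeps power 0.951. At ρx/ρy of 0.05/0.10 and 0.10/0.20 it is about 0.96 and 0.97. The unadjusted test is not protected in the same way: its simulated type I error at N = 129 is about 5% at 0.05/0.05, 7% at 0.10/0.10 and 14% at 0.20/0.20.

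**The case against.** The strongest reply is that power need not suffer. A random intercept removes between-hospital outcome variance, so it can match or exceed 0.95, as Step 4 shows. A simulation that estimated the ICC gave 0.936, 0.927, 0.915 and 0.856 at the four settings in the table, against 0.937 without clustering, although with type I error of 5% to 7%. This stands. A reader might infer that any valid hospital-adjusted analysis has less than the stated power; that is not true in general. Nor can power from a variance-inflation formula for least squares, 1 + (m − 1)ρxρy, serve as the power of an adjusted model.

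A reader might also infer that the study is severely underpowered. The documents do not support this. No ICC is given, the four tabulated settings all give the predictors the larger ICC, and the Bias control section asserts similar workloads across the hospitals. If all 155 were analysed there would be more reserve. However, 155 is meant to absorb dropout, and a larger sample does not cure the type I error, which is about 6% to 19% at 155 under the same four settings.

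A third tempting reading is that a null result for noise annoyance would wrongly claim 95% power because of clustering. The 0.95 belongs to the overall four-predictor test. It was never power for the noise-annoyance coefficient, even with independent nurses.

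Finally, the survey began in March 2023, so a restated power no longer guides recruitment. That is fair, but the analysis model can still be changed, and the type I error arises there.

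**Conclusion.** The point holds in a limited form. The arithmetic behind 129 is right. What fails is the unconditional assurance: 0.95 power and 5% alpha hold together only if within-hospital correlation in the predictors or the outcome is near zero, and nothing in the article establishes that. The similarity of workloads claimed under Bias control comes without a figure and does not address shared noise.

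The clearer damage is to type I error under the planned unadjusted analysis, about 6% to 17% at N = 129 over the tabulated settings and close to 5% if both ICCs are about 0.05. Power after adjustment depends on the model chosen: from about 0.95 to 0.87 with a random intercept, and from about 0.91 to 0.69 with fixed effects. All these sizes rest on assumed ICCs, equal hospital sizes and the simplified predictor structure in the working. The true size cannot be fixed from the documents.

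**What to change.** Two linked changes are needed; rewording the sample size text alone would leave the type I error as it is.

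1. **Statistical analysis section.** Account for hospital in both the regression and the mediation analysis, for example with a hospital random intercept, or with cluster-robust errors and a small-sample correction suited to 11 clusters. Name the model. Hospital fixed effects are also valid but cost more power at the tabulated settings.
2. **Participants section.** Keep the planned size. Say that 0.95 assumes independent nurses. Replace the closing assurance with power for the overall four-predictor test under the named model, over a stated ICC range that includes cases where the outcome ICC is the larger. Commit to reporting the observed ICCs.

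The cost is a short recalculation, a change of wording and a different model specification, with no extra participants. The downsides are slightly wider intervals and possibly a less favourable quoted power. The change requires that each questionnaire can be linked to its hospital, which the article does not state and which should be confirmed.
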